## Abstract

**Background:**

Intimate partner violence (IPV) is a leading threat to women’s health and safety globally. Women in abusive relationships make critical decisions about safety and harm reduction while weighing multiple competing priorities, such as safety of children, housing and employment. In many low- and middle-income countries (LMIC), IPV prevention and response services are limited and women lack access to safety planning resources. In high-resource settings, an interactive safety decision aid app (myPlan) has been found valuable in reducing decisional conflict and empowering women to take action in accordance with their safety priorities. This paper describes 1) the community-participatory formative process used to adapt the myPlan app content, interface, and implementation for the Kenya context, and 2) the randomized clinical trial study protocol for efficacy evaluation of myPlan Kenya.

**Methods:**

A community-participatory formative process engaged service providers and stakeholders, as well as IPV survivors for adaptation, followed by an in-depth pilot and final refinements. A randomized clinical trial design will then be used to determine efficacy of the myPlan Kenya app compared to standard care among women reporting IPV or fear of partner and living in an urban settlement. myPlan Kenya app provides and solicits information on a) relationship health; b) safety priorities; and c) severity of relationship violence. Based on the woman’s inputs, the evidence-based algorithm developed for myPlan Kenya generates a tailored safety plan. Outcome measures are assessed at baseline, immediate post-intervention, and 3-month post-baseline. Difference-in-differences analysis compares primary (e.g. safety preparedness, safety behavior, IPV), and secondary outcomes (e.g. resilience, mental health, service utilization, self-blame) across timepoints by group.

**Discussion:**

Formative phase revealed high feasibility and acceptability of a technology-based intervention for safety planning in this LMIC setting. This phase generated essential refinements to myPlan Kenya app readability, content and implementation, including increased visualization of messaging, and implementation via community health volunteers (CHVs). The resulting trial will be the first to evaluate efficacy of a community-partnered technology-based IPV intervention in a LMIC. Our adaptation process and trial results will inform researchers and interventionists to integrate multiple data sources to adapt IPV intervention content and interface in settings where technology-based interventions for IPV are novel and literacy is limited.

**Trial registration:**

Pan African Clinical Trial Registry approval received 25 April 2018 (PACTR201804003321122); retrospectively registered.

## Background

Globally, intimate partner violence (IPV) is a persistent threat to the health and wellbeing of women and girls. Eliminating IPV and other forms of gender inequity are targets of the Sustainable Development Goals [1]. Non-fatal consequences of IPV include poor mental, physical, and sexual health [2–10]. Over one third of female homicides globally are perpetrated by an intimate partner; and this proportion is on average six times higher for women relative to men [11]. In Kenya, national data from 2014 indicates that 39% percent of ever-married women age 15–49 have ever experienced spousal physical or sexual violence, relative to 9% of ever-married men in the same age group [12]. The prevalence of IPV is even higher in Nairobi’s informal settlements, and confers profound consequences to physical, sexual and mental health [13]. Social norms create a culture of IPV tolerance that challenges women’s ability to seek help or identify their experiences as abuse [14, 15]. Practices such as dowry payment for marriage contribute to strict social norms of gender inequity including the dominance of male partners on decisions related to sex, control, and authority in the relationship, regardless of the woman’s desires or preferences [16–19]. Comprehensive efforts to prevent and respond to IPV are urgently needed, particularly in low- and middle-income countries (LMICs), where IPV support resources can be scarce.

Safety planning is one of the most widely recommended interventions to prevent and respond to IPV. Disclosing abuse and obtaining support is beneficial [20–22], and can reduce post-traumatic stress [22], self-blame [23], and revictimization [24–26]. Too few survivors receive this support due to shame, self-blame, concern about stigmatization, and lack of knowledge about services [27–29]. Women also often face multiple, competing priorities in considering how to respond to IPV, with priorities including children, privacy, and financial security. Decision aids are an established tool in healthcare settings for providing information about options and clarifying personal priorities in order to make treatment decisions. The first decision aid to specifically address IPV-related decision-making and safety planning is *myPlan*, an interactive, personalized app developed by Johns Hopkins University (JHU) (www.myplanapp.org).

The myPlan interactive app provides education on healthy relationships, and solicits information about current intimate relationship, including risk of severe and lethal violence in the relationship and safety priorities to prompt recognition of risk and generate safety strategies tailored to women’s priorities, including referrals for support [30–32]. Key features of the app include the interactive “red flags” for unhealthy relationship and the Danger Assessment (DA), a measure of risk factors for severe and lethal violence in abusive relationships [33], with an instant score converted to danger level. An interactive visual aid enables prioritization of safety priorities (e.g. health and well-being of children, having resources, privacy) via systematic pair-wise comparison using a clickable “sliding bar” for the user to rank priorities. Based on input data, a personalized safety plan with relevant referral information is generated from the evidence-based algorithm designed for the app. As it is common for abusive partners to monitor survivors’ digital activities, myPlan safety features include: 1) a 4 digit security PIN for logging in; 2) instructions for entering a “dummy” PIN that takes the user to alternate content (in this context a cooking website was deemed most appropriate) if the app is discovered and they are forced to log in; and 3) access via web or downloadable app, allowing users to choose the safest method of access.

myPlan draws on elements of social cognitive theory [34], Dutton’s empowerment model [35] and trauma-informed care (TIC) [36, 37], which emphasize safety and empowerment through decision-making and healing. myPlan provides support for 1) defining healthy relationships, with descriptions of behaviors that are not healthy; 2) safety strategies, by helping women identify the severity of the violence and potential danger to self and family, 3) decision-making, via identifying safety priorities (e.g., privacy/confidentiality, children, feelings for partner) and thus reducing decisional conflict and enhancing safety preparedness, and 4) healing via validating messages to counter the culture of victim-blaming, further bolster resilience, and enable safety behavior and connection to both formal (e.g. hotline, health care providers, advocates) and informal (family/friends, co-workers) support services, thus ultimately enhancing health and reducing violence.

Women who have used myPlan have found it a unique opportunity to privately consider safety priorities, receive information about danger in relationships, and serve as an ongoing accessible resource for safety. In trials in high-resource settings, women that used myPlan reported reductions in decisional conflict about safety and increased use of helpful strategies that promoted health, safety, and well-being [38]. They were also more likely to leave an abusive relationship than those in the control group [38], though it is well-understood that leaving an abusive relationship is not always feasible or preferable, nor does it ensure safety. myPlan has been implemented in a range of high resource settings (e.g. USA, Canada, New Zealand, and Australia) with women of all ages [31, 39, 40].

Deploying this technology in LMICs requires formative work and collaboration with community partners and survivors to determine feasibility and acceptability of the content and delivery as well as rigorous evaluation. To advance the global priority of evidence-based interventions for women in LMICs that prevent IPV and mitigate its health impact, and cross-validate an app that have been developed in other settings, our team conducted extensive tailoring of the myPlan app for a LMIC setting (Nairobi, Kenya). This paper describes 1) the adaptation process, and 2) the study protocol for the efficacy evaluation of myPlan Kenya. This paper describes the contextual considerations necessary to ensure transferability of the myPlan app to IPV survivors in urban informal settlements of Nairobi, while maintaining consistency with intervention components found effective in other settings. The protocol is approved by the Johns Hopkins Bloomberg School of Public Health Institutional Review Board (IRB) and the Kenya National Commission for Science Technology and Innovation, and registered with the Pan African Clinical Trial Registry as PACTR201804003321122. This study did not assemble an independent data monitoring committee because the follow-up duration was relatively short, and because the majority of study enrollment was completed prior to obtaining follow-up endpoints. Interim results were reviewed at regular intervals by the investigative team; specifically the team reviewed IPV prevalence and mental health indicators.

### Community-partnered participatory research & study setting

All research was conducted in close collaboration with Ujamaa-Africa, a non-governmental organization (NGO) based in Nairobi, Kenya focused on violence prevention and response. The Mashinani department of Ujamaa provides economic empowerment to IPV survivors via support groups coupled with microfinance loans, affording the team unique insight into local IPV dynamics. The six-member Mashinani team led the implementation of the formative phase and randomized controlled trial (RCT), in close collaboration with the Johns Hopkins University (JHU) research team.

This study was conducted in three informal settlements in Nairobi, Kenya: Korogocho/ Kariobangi, Dandora, and Huruma/Mathare. The field office was the secure Mashinani office headquarters in Kariobangi North. Two other informal settlements, Dandora and Huruma/Mathare, were chosen for their geographic and economic diversity, as well as the established rapport of Mashinani in these communities.

## Formative phase to tailor app content and Interface for feasibility, Relevance & Acceptability

The formative phase was conducted from May to December of 2017. Community stakeholders and violence prevention/response practitioners were engaged for key informant discussions (KIDs), and adult (18 years or older) IPV survivors were recruited for focus group discussions (FGDs), all recruited via purposive, community-based sampling in collaboration with Ujamaa Mashinani team.

### Key informant discussion and IPV survivor focus group discussion data collection

Key informants are community health volunteers (CHVs), chiefs or leaders, and other service providers working with IPV survivors in the targeted settlements. Key informants were identified via engagement with local IPV organizations. Key informants were eligible if they were 18 years or older, had experience working directly with female IPV survivors in Nairobi and provided informed consent*.* FGDs were conducted with IPV survivors. FGD participants were recruited primarily through word-of-mouth, supported by flyers and presentations at local organizations and chief offices. Eligible women were 18 years or older, had experienced physical, sexual, or emotional violence by a current or former partner in the past 12 months. Recruitment continued until repetition of themes (saturation) was achieved [41].

KIDs and FGDs with IPV survivors lasted approximately 90 min and were conducted in private locations. Data collection was conducted by a team of three female Kenyan interviewers in English and Swahili. Interviewers received two weeks of qualitative research training prior to study implementation, including mock sessions. On-site support from a seasoned qualitative researcher was available.

Following a semi-structured guide, the KID and FGDs were designed to inform the myPlan Kenya app content, interface, and implementation. Content-related probes centered on women’s experiences of violence, recommended and utilized harm reduction and safety strategies, community norms and beliefs about IPV, and availability of community resources for IPV survivors. Interface and implementation-related probes centered on feasibility, design, and use of smartphones for delivering the app with women in the local area. Mock designs of the app were color-printed on large, laminated pages to appear as screen shots of each app component. They were used to solicit feedback from participants on appearance, content and user experience. Key informants were additionally asked about IPV support services; study team members met with organizations recommended during KIDs to understand scope of services and assess fit as a participant referral within the app, and during the subsequent RCT referral.

### Key informant discussion participants

A total of 16 key informants participated in seven semi-structured KIDs of three to four participants. Two key informants completed individual discussions due to logistical constraints. KID participants were primarily female (*n* = 15 female, *n* = 3 male) and averaged 9.7 years of work experience with IPV survivors. Roles included: four social workers, five CHVs, one chief, two psychosocial therapists or counselors, two advocates focused on gender justice, and four NGO employees who worked directly with survivors.

### IPV survivor participants in focus group discussions

After informed consent, the majority of the survivors participated in one of six semi-structured FGDs, with an average of eight per group. One survivor opted for an individual interview for privacy. FGD participants had a mean age of 32.3 (SD = 12.6). Approximately 30% identified as Kikuyu and Luhya, with fewer identifying as Luo (14.3%), Kamba (14.3%), Borana (4.1%), and Meru (4.1%). Nearly 80% of women were in a current relationship and had on average two children (SD = 1.6). Almost half (49.0%) of survivors reported past month physical violence and 36.7% reported past month sexual violence.

### Qualitative analysis & triangulation of input from multiple sources

All qualitative data were audio-recorded, transcribed, translated verbatim from Swahili to English, and quality checked by a team of six transcribers. Three Masters-level research assistants coded all interviews in Atlast.ti.1.6 using inductive thematic analysis. To improve internal consistency, multiple team member checks and revisions were performed. Mashinani staff engaged in data interpretation via participatory triangulation of data facilitated by weekly team debriefs with the on-site field researcher, lead investigators, and Mashinani staff. Field notes were maintained and referenced for triangulation of data. Triangulation of results across IPV stakeholders and survivors occurred via convergence matrices which displayed key findings across data sources to identify areas of agreement, partial agreement, silence, or dissonance [42].

### Pilot testing of the refined myPlan Kenya app

The myPlan Kenya app was adapted based on input gleaned from IPV survivors and stakeholders as described above. In cases of dissonance, silence, or partial agreement, recommendations prioritized the input of IPV survivors. All content was translated into Swahili and reviewed by native speakers for comprehension. The resulting myPlan Kenya app was pilot tested with 18 IPV survivors in December 2017. Participants tested the app and completed an in-depth interview with trained research assistant to clarify feasibility and acceptability. Pilot testing and interviews lasted approximately 90 min and were conducted one-on-one in a private setting. Structured notes were taken to inform updated convergence matrices and finalize intervention format and implementation.

### Summary of intervention app adaptations and their rationales (Table 1)

#### Content

The primary content adaptations centered on safety strategies to reflect women’s realities, including the social pressures for partnership preservation and childbearing. The formative phase identified domains of safety strategies that required development and refinement. Primary examples included child safety strategies in the moment of conflict, as well as options for women to temporarily leave the home and visit family to stay safe or gain leverage for partner changing his behavior. The myPlan app does not recommend staying or leaving a given relationship but rather provides tailored strategies for safety that were adjusted as recommended by survivors and key informants to emphasize harm reduction to “stay safely” rather than leave the relationship, in response to the strong social stigma against relationship termination in this setting.

**Table 1 Tab1:** Summary of formative phase results and corresponding adaptations to content, interface and planned implementation strategy

		**Source(s)**			
**Qualitative Finding/Rationale**	**Intervention Adaptation**	**FGD**	**KID**	**Intervention adaptation leadership field team** **(Mashinani)**	**Pilot**
**App Content**					
Leaving relationship safely not considered feasible in this setting	Emphasis on harm reduction strategies for “staying safely” in relationship	X			
Strong local preference and pressure to endure violence		X			
Cultural norms and relationship dynamics with in-laws and natal families	Development of temporary leaving strategies to natal family home and in-law home	X		X	
Permanent separation from partner not considered feasible in this context		X		X	
Preference for short-term options that do not compromise family status in the community		X			
Parental stress over children exposed to violence	Addition of age-specific child safety strategies, and sexual/reproductive health safety strategies	X			
Distinct cultural and tribal norms around child custody		X	X	X	
Concern for risks and harms incurred during pregnancy		X			
Pressure specific to childbearing and care for children		X		X	
Fear of community stigma around violence	Modification of ‘priorities’, ‘healthy relationships’, and ‘harmful beliefs about abuse’ section of the app to reflect those in this context	X			
Pressure specific to childbearing and care for children		X		X	
Common beliefs and myths regarding healthy and unhealthy relationships in this context		X	X	X	
Participant challenges interpreting the danger assessment (homicide risk assessment)	Danger assessment result presented to participants as a binary (increased danger vs. variable danger) for simplicity				X
**App Interface**					
Time needed to review and complete each app component app negatively impacted feasibility and engagement	Components of app re-organized and shortened where possible			X	X
Preference to use sliding scale for ordering personal priorities	Rank system removed and replaced with sliding scale for ordering personal priorities				X
Wide range of literacy including low literacy	Inclusion of graphics and short animations			X	X
**App Implementation**					
Women’s familiarity with apps is limited though growing	Community health volunteers (CHVs) trained to facilitate app implementation		X	X	X
Women may lack confidential space to use the phone without arousing suspicion		X			
Phone-sharing is common		X			
Quality of phones and ability to support apps is limited in some areas, though expanding			X	X	

#### Interface and implementation

Participants suggested CHVs could help orient women to the app to maximize feasibility, acceptance, and impact. This recommendation was adopted for the resulting RCT protocol, which engaged CHVs for recruitment, data collection, implementation of intervention app and control condition, interpretation of results, and dissemination.

Pilot test feedback centered primarily on app format and implementation. The initial refined app was too lengthy, taking 1.5–2 h to complete. Participants recommended streamlining the app content for brevity, to allow for full engagement with each component. Graphics and animated videos were recommended for readability and interactive support, and were developed and finalized with extensive input from the Mashinani team. Following the pilot phase feedback, safety strategies were positioned earlier in the app process for accessibility. Participants also advised the content of the safety strategies be more tailored to women’s personal circumstances, particularly regarding child safety and leaving strategies.

## Randomized controlled trial methods

### Design

This trial is designed as a randomized, controlled, participant-blinded superiority trial with two parallel groups (1:1 allocation ratio), with primary end points of safety preparedness, decisional conflict (e.g. clarity of values, knowledge), use and helpfulness of safety strategies, and IPV.

We hypothesized women in the myPlan Kenya safety decision app group would have increased safety preparedness, reduced decisional conflict about safety priorities, increased helpfulness and use of safety behaviors, and reduced IPV at three-months post-baseline in comparison to the control group.

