## Measures

### Primary outcomes

Primary outcomes include safety preparedness, decisional conflict, use and helpfulness of safety strategies, and IPV.

A 10-item scale assessed safety preparedness immediately following completion of intervention or control condition. Items focused on the value of the reviewed material for readiness in decision-making and weighing of risk/benefits, e.g., “to what extent did the material prepare you to make safety decisions,” with participants indicating preparedness on a Likert scale (Responses: 0-Not At All to 4-A Great Deal; Range: 0–40; modelled continuously).

A 12-item adaptation of the Decisional Conflict Scale (DCS), which discriminates those who make decisions and those who delay [44], asked participants to rate their knowledge, clarity and confidence in safety options and risk/benefits of potential options on a Likert scale [30] (Responses: 0-Not At All to 4-A Great Deal; Range: 0–48; modelled continuously).

Use of safety strategies was assessed through five-item index of strategies specific to content area covered in the app; the index was adapted from previous myPlan trials and formative work in the U.S. [26, 30, 45] Specifically, participants were asked “In the past three months, have you: 1) Left the house temporarily to put space between you and your partner; 2) Developed an emergency signal to use with others when you felt you were in danger; 3) Put a plan into place for how to keep your children safe; 4) Begun saving money to build self-sufficiency; and 5) Been part of a loan savings group in order to improve your family’s financial situation. If used, participants were then asked to rate the helpfulness of the strategy on a Likert scale (Responses: 1-Not Helpful to 5-Very Helpful). Responses generated two summary metrics: use of safety strategies reflecting number of strategies used (Range: 0–5), and helpfulness of strategies used, reflecting both use and helpfulness by dividing summed helpfulness by number of strategies used (Range: 0-Never Used to 5-Used and Found Helpful).

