Longer-term outcomes focused on IPV experiences. Physical and sexual IPV were assessed through the short forms of the Revised Conflicts and Tactics Scale (CTS-2) [46]. For each of ten violent behaviors, women were asked frequency of occurrence in the past 3 months: Never (0), 1–2 times (1), 3+ times (2), and scores summed across behaviors (Range: 0–20); IPV will be examined as both continuous and binary for physical IPV only, sexual IPV only, and combined physical and sexual IPV. The Women’s Experiences of Abuse (WEB) Scale [47] captured the lived experience of abuse (Responses: 1-Agree Strongly to 6-Disagree Strongly; Range: 10–60). Reproductive coercion was assessed via existing 9-item measure [48, 49] deemed appropriate based on formative research and summarized into a binary measure indicative of experience/no experience. All IPV assessments used behavioral definitions in accordance with best practices [43].

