## Data analyses

Prior to analyses, data quality will be examined through descriptive statistics, including tabulations and distributions to assess missingness. Imputation will be used for variables with missingness < 10%. Differences in intervention and control groups will be assessed for outcomes and potential confounding variables using Chi-square tests (categorical variables) and t-tests/ANOVA (continuous variables). Significance will be set at 5%. All analyses will account for site and within-person clustering. Attrition analysis comparing key demographics and baseline indicators across those lost-to-follow up with those retained will identify potential biases in the final retained sample.

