### Statistical power

As decisional conflict estimates were unavailable for target population, the study powers on IPV; 2014 Kenya national data estimate 39% lifetime IPV prevalence for women [12]. Setting alpha = 0.05 and power to .80, a study with 175 intervention participants and 175 controls will find a significant difference between the groups if 25% of women experience violence in the intervention group compared to 39% in the control group [57]. If attrition rate is 15%, we will be able to detect significant difference if 24% of the intervention group experiences IPV.

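### Five parallel primary outcomes, with the IPV version left open, are each judged at p < 0.05 without ordering or adjustment

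*Protocol article*

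**What the plan says.** The Design section describes a superiority trial "with primary end points of safety preparedness, decisional conflict (e.g. clarity of values, knowledge), use and helpfulness of safety strategies, and IPV". The Primary outcomes section repeats the list: "Primary outcomes include safety preparedness, decisional conflict, use and helpfulness of safety strategies, and IPV". Neither place ranks the outcomes or says that all must succeed.

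The same section then expands two of the headings:

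- Safety strategies: "Responses generated two summary metrics: use of safety strategies reflecting number of strategies used", and a second metric for helpfulness.
- IPV by CTS-2: "IPV will be examined as both continuous and binary for physical IPV only, sexual IPV only, and combined physical and sexual IPV".
- Two further measures follow: the WEB scale, which "captured the lived experience of abuse", and reproductive coercion, "summarized into a binary measure indicative of experience/no experience".

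The Data analyses section fixes the level ("Significance will be set at 5", in per cent). The Intervention efficacy section fits arm, pre/post status and their interaction for each outcome, and takes an interaction p-value below 0.05 as showing an intervention effect. Under Statistical power, "the study powers on IPV", because no decisional conflict estimates existed for this population. That calculation spends the full 5% on a single comparison of proportions.

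**The concern.** The stated rule gives every primary outcome its own 5% test and lets each significant one stand as evidence of efficacy. With five outcomes, and several ways to score one of them, a significant primary result is much more likely under no effect than the 5% used in the power section.

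The open IPV definition adds to this. The same CTS-2 items can be reported as a score or as any/none, and for physical, sexual or combined violence. Nothing says which of these answers the IPV hypothesis, so emphasis could follow the data. The power statement does not settle it: it says only IPV, and its 39% is a national lifetime figure.

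At stake is whether one significant primary result can carry a claim that the app works.

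**Working it through.** **1. The plan's own figure.** Inputs (Statistical power): 39% v 25%, alpha 0.05, power 0.80, 175 per arm. The protocol does not state whether the test is two-sided; two-sided is assumed here. Pooled-variance formula, mean proportion 0.32:

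n = [1.960·√(2·0.32·0.68) + 0.842·√(0.39·0.61 + 0.25·0.75)]² / 0.14² ≈ 174 per arm.

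Power at 175 per arm is 0.804. With 15% attrition (175 × 0.85 ≈ 149 per arm), 39% v 24% gives 0.799. Both statements reproduce, each with one test at the full 5%.

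**2. How many tests.** Named outcomes: preparedness, decisional conflict, use, helpfulness, IPV = 5. Broadest reading: the first four, plus 3 × 2 = 6 CTS-2 codings, plus WEB and reproductive coercion = 12.

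**3. Chance of at least one false significant result.** If independent, this is 1 − 0.95^k. The documents give no correlations, so the other columns assume one common correlation (multivariate normal simulation, 400,000 draws).

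| Tests | Independent | 0.3 | 0.5 | 0.7 |
|---|---|---|---|---|
| 5 | 22.6% | 20.8% | 18.2% | 14.8% |
| 12 | 46.0% | 39.8% | 31.9% | 23.2% |

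A structured pattern is more realistic for the twelve. Assume 0.5–0.9 among the CTS-2 codings, 0.2–0.6 between these and WEB or coercion, and 0–0.3 elsewhere. The result is 29–41%.

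**4. Only results favouring the app.** Each two-sided 5% test leaves 2.5% on that side:

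- 5 tests: 1 − 0.975^5 = 11.9%
- 12 tests: 1 − 0.975^12 = 26.2%
- one test: 2.5%

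**5. Cost of control.** For 39% v 25% with 175 per arm, by the formula in step 1:

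| Alpha for IPV | Power | Per arm for 80% |
|---|---|---|
| 0.05 | 80% | 174 |
| 0.05/5 = 0.01 | 59% | 258 |
| 0.05/12 = 0.0042 | 48% | 304 |

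Five tests at 0.01 give 1 − 0.99^5 = 4.9% if independent. Under Holm, IPV is tested at between 0.01 and 0.05, so its power lies between 59% and 80%. These are powers for two proportions, as in the protocol; power for the interaction term was not computed.

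**The case against.** **The article is condensed, and multiplicity is often left to the SAP.** True in general. Here, however, the article itself states the decision rule for each test. An SAP with a hierarchy or adjustment would replace that rule, not fill a gap. The objection does not remove the point.

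**Twelve is not the protocol's number.** This stands. A reader might infer twelve declared primary tests and a 46% chance of a false efficacy claim. The documents do not support that. Both formal lists name five. The six CTS-2 versions are to be examined, which does not make each a separate primary test. WEB and reproductive coercion are in neither list, although they are described under the primary heading. Independence is also impossible for codings built from the same items, and the 46% counts false harm as well as false benefit.

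**The interaction rule may not reach preparedness.** This stands. Preparedness is described only as measured straight after the app or control content, with no baseline value. On the broadest reading that leaves 11 interaction tests (1 − 0.95^11 = 43% if independent), plus one post-only test at the general 5% level.

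**Each hypothesis is prespecified, directional and keeps its own 5% error.** Also true, and no passage says that one success makes the trial positive. It would therefore go too far to say that no confirmatory claim is possible. What is lacking is control over the set when any one result may be presented as efficacy.

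**Sizing on IPV does not make it the gatekeeper.** Correct. IPV was used for sizing because decisional conflict estimates were missing, and neither its version nor a recall window is fixed there. If IPV had to succeed first, the other four claims would be blocked with 20% probability even at the planned effect. Testing IPV at follow-up alone would also depart from the stated difference-in-differences analysis.

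**Conclusion.** The point holds in this form: five outcomes share primary status, the IPV version is not fixed, and each test is read at an unadjusted 5%.

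- Five named outcomes: about 15–23% chance of at least one false significant result in either direction (15% at an assumed correlation of 0.7, 23% if independent).
- Up to twelve tests: about 23–41% under the assumed correlations, with 46% as a ceiling that overlapping codings cannot reach.
- False results favouring the app only, if independent: 12% and 26%, against 2.5% for one test.

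The correlations are assumptions, and twelve is the broadest reading of the text. The conclusion depends on neither: the lowest either-direction figure shown, 15%, is about three times 5%.

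**What to change.** 1. **Fix the IPV outcome.** Name one binary version, to match the proportion-based power calculation; for example, any physical or sexual IPV in the past 3 months. Analyse it by the stated arm-by-time interaction. Make the other CTS-2 codings, WEB and reproductive coercion supportive, with confidence intervals and no significance claim.
2. **Control the error over the five primaries**, by one of two routes:
   - (a) Holm at an overall 5%. All five stay primary. The cost is IPV power of between about 59% and 80% for 39% v 25% with 175 per arm, which should be restated in the power section.
   - (b) IPV as the sole confirmatory primary at 5%, which keeps the stated 80%. The other four become secondary, tested with Holm among themselves. The cost is that they then support no primary claim, and the text should say so openly.
3. **State the test for preparedness**, since the interaction model may not apply to it.
4. **Date the change.** The Background section reports that the team reviewed interim IPV prevalence. The amendment should say so and be made before any comparison by arm.

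No new data are needed, but the choice between (a) and (b) gives up either some IPV power or the primary standing of four outcomes.
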